**Fig. 2 Fig2:**
[figure not shown]
CONSORT statement

## Results

### Selection and recruitment of local ophthalmologists and patients

Since local ophthalmologists will assess the need for the intervention, they will decide which patients to include in the study. The ophthalmologist will inform all patients who would receive inpatient monitoring of IOP as standard care about the SALUS study. There will be no selection based on severity of illness or criteria other than the inclusion and exclusion criteria of the study (Table 1).

In general, every ophthalmologist in Westphalia-Lippe will have the opportunity to participate in the project. The recruitment of ophthalmologists appears to be particularly effective with a good cost–benefit ratio. Those with a high number of glaucoma patients are preferentially recruited, not least because such practices are likely to enroll the most patients in the study. The work involved should be communicated to the ophthalmologists in an easily understandable and concise manner, while any further effort on their part should be kept to a minimum. The ophthalmologist should be able to access information at self-selected times. The trial will be brought to the attention of the ophthalmologists mainly via e-mails, letters, information events, website, and articles. Participating ophthalmologists will get a detailed study folder with all relevant documents and a guideline for briefing the glaucoma patients to make the procedures standardized. They can also attend optional training sessions.

Patients will be informed by project flyers or addressed directly by the physicians. An information hotline will be available on weekdays for all interested parties. High drop-out numbers are not expected for patients assigned to the CG, as they will receive services that are current standard care. There is just one additional appointment at the end of the study period, which is the final examination in the eye hospital. It is assumed that the patients will take advantage of this, on account of the intensive care and additional review of their disease and medication, which could help to avoid further complications and the risk of blindness.

### Data management and monitoring

The ECF has been developed for collecting and managing the patient’s primary data that can be accessed by the local ophthalmologists, hospitals, and the study participants. The eye hospitals will be responsible for the care of their regionally assigned patients. As stated above, the patients will be automatically randomized and patient-specific informed consents will be created by the system.

At predefined points in time, the primary data collected in the ECF and secondary data provided by the participating health insurance companies, both required for evaluation of the study, will be transmitted end-to-end in encrypted form to the trust center at Bielefeld University, which will act independently from the evaluating center. The data will then be pseudonymized, merged, and forwarded to the evaluating center.

For quality assurance, monitoring and grading of images and data will be necessary and will require evaluation by several physicians at a reading center. Typically, one physician will act as junior reader and the other as senior reader to uphold the four-eye principle. In case of doubt, reader A and reader B can each serve as junior reader. In the SALUS project, a glaucoma specialist and a senior resident will be responsible for the grading of diagnostics. During grading, the OCT and HRT images (if available) from the initial and final examination after 12 months will be evaluated with regard to the required outcome parameters (RNFL, BMO-MRW) for each patient group. In addition, the completeness and plausibility of further examination results from the hospital and from the participating local ophthalmologist (IOP, blood pressure, perimetry) will be checked.

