### Intervention

The main part of the intervention is outpatient monitoring of IOP using a self-tonometer. The glaucoma patients who qualify to participate in the study will be briefed by the local ophthalmologist about the study design as well as the benefits and risks and asked to sign an informed consent form. After randomization, they will be contacted by the Department of Ophthalmology of the University of Muenster Medical Center to arrange an appointment at one of the participating eye hospitals for an initial examination.

The initial examination includes IOP measurement to investigate the pathological pressure peaks, a 30° visual field examination, an OCT of the optic nerve head, a Heidelberg retina tomography (HRT) (if available), and a questionnaire about health-related quality of life. Subsequent to the initial examination, patients will be instructed by the clinical staff in the functioning and handling of the IcareHOME® self-tonometer and 24-h blood pressure measuring device. The patients of the IG will then receive the devices and perform self-tonometry over the course of seven days. They will also undergo initial blood pressure monitoring for 24 h, starting at the end of the training. The IOP and blood pressure values measured will be evaluated by the local ophthalmologists, who can adjust the patient’s therapy on the basis of the results. Thereafter, check-ups will be carried out every 3 months by the local ophthalmologists. The final examination will be performed 12 months after the initial examination at the same participating eye hospital and will replicate the initial one but end with a final interview between the doctor and patient.

All measured values, the medical history, and the imaging performed will be transferred by the local ophthalmologists or hospitals to an electronic case file (ECF), a cloud-based system for the management of the patient’s primary data. The ECF can also be used to raise queries with a glaucoma specialist and senior resident from the University of Muenster Medical Center. IG participants will also have access to the ECF and be able to view all measurement data. The participants will gain a comprehensive insight into their disease progression for the first time and will also become more involved and informed about treatment options.

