### Randomization

After informed consent, patients will be randomized 1:1 into the IG and CG. The randomization will be generated automatically by the ECF after the local ophthalmologist has submitted the patient’s master data (year of birth, sex, and three digits of the zip code) and eligibility criteria in a web-based form. The underlying randomization sequence will be known only to the developers of the ECF (Fraunhofer Institute for Applied Information Technology FIT) who will act independently of the personnel analyzing (Bielefeld University) and conducting (University of Muenster Medical Center) the study. This sequence will be concealed from all study staff so that it cannot be manipulated by physicians, clinical staff, or the patients themselves.

Participants will receive a study identification number after randomization and their assignment to one study group. Owing to the nature of the intervention, it will not be possible to blind either the patients, the personnel conducting the study or the healthcare providers. The independent evaluators of the study will be blinded during the study by being provided solely with a pseudonymized data set for data analysis.

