## Discussion

The SALUS study is the first randomized, controlled prospective clinical trial to investigate the effectiveness of self-tonometry. The healthcare situation of glaucoma patients could be improved by the measuring of IOP over several days, especially in rural, structurally disadvantaged areas and those with fewer specialist health services.

In this study, patient-input is integrated into the diagnosis and treatment plan. It gives patients comprehensive insights into the course of their disease and promotes compliance. If self-tonometry is established in regular patient care as a result of SALUS, this could reduce the need for inpatient hospitalization. On the one hand, this would free up capacity in hospitals, and on the other hand, it would provide more comfort for patients, i.e., bring benefits without requiring extra effort or absence from work. The fact that patients could then remain in their accustomed domestic environment and daily routine is expected to improve their quality of life. They may save travel costs and would not be unnecessarily exposed to the risk of infection, especially in times of a pandemic. The taking of IOP measurements at a series of times predefined by the study will enable therapy to be optimally adjusted, and complications arising from delayed adjustments to therapy or more complex operations could possibly be avoided. The long-term benefit could be less blindness due to glaucoma. The telemedical focus could significantly improve healthcare by making medical services available independent of time and space. Telemedical networking via the cross-institutional ECF could optimize collaboration between the areas of healthcare provision and service providers. The ophthalmologist could rely on the support of continuously improving, self-learning algorithms in the evaluation of findings and therapy decisions, thus optimizing treatment strategies. Through digital networking, repeat medical examinations could be avoided when treatment of a patient takes place in another treatment center. The local ophthalmologists will be professionally supervised by a glaucoma expert and a senior resident and have the opportunity to base their treatment on an improved database.

Healthcare costs could be reduced by saving hospital resources. Once incorporated into standard care, economies of scale could lower prices further. Moreover, the fixed and implementation costs could be spread over a greater number of patients.

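### The outcome OCT/HRT images are graded, with no stated masking to arm, by the same pair of roles that advises on and supervises patients' care

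*Protocol article*

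**What the plan says.** Four sections of the Protocol article bear on this.

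- **Data management and monitoring.** On grading: "a glaucoma specialist and a senior resident will be responsible for the grading of diagnostics". The OCT and HRT images from the initial and final examinations "will be evaluated with regard to the required outcome parameters (RNFL, BMO-MRW) for each patient group". The same paragraph adds that "the completeness and plausibility of further examination results from the hospital and from the participating local ophthalmologist (IOP, blood pressure, perimetry) will be checked".
- **Intervention.** "The ECF can also be used to raise queries with a glaucoma specialist and senior resident from the University of Muenster Medical Center".
- **Discussion.** "The local ophthalmologists will be professionally supervised by a glaucoma expert and a senior resident".
- **Randomization.** The Muenster centre is named as "conducting (University of Muenster Medical Center) the study". On masking, "it will not be possible to blind either the patients, the personnel conducting the study or the healthcare providers". The one group with masking is this: "The independent evaluators of the study will be blinded during the study by being provided solely with a pseudonymized data set".

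Under Secondary endpoints, RNFL thickness is taken from OCT, and rim volume and rim area from HRT where available, at the initial and final hospital examinations.

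**The concern.** In an open trial, patients and clinicians know the allocation, but someone reading an optic nerve image need not. Masked reading is therefore the main protection available for the structural outcomes. Here the grading goes to roles that also answer questions about individual patients and oversee the treating ophthalmologists, and nothing in the article separates the two tasks. A reader who has advised on a patient may know the arm and the clinical course when judging the 12-month image against the initial one. Differences between arms in RNFL thickness, BMO-MRW or rim parameters could then partly reflect the reader's expectation. Blinding the evaluators does not remove this, because they can only analyse the grades they are given.

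**Working it through.** The point concerns roles and masking, so the check sets the sections side by side. Arithmetic enters only for scope.

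1. **Who grades and who advises.** Data management and monitoring names a glaucoma specialist and a senior resident as graders. Intervention names a glaucoma specialist and senior resident, at Muenster, as the contact for ECF queries. The Discussion names a glaucoma expert and a senior resident as supervisors of the local ophthalmologists. The descriptions match in all three places. That the same individuals are meant is a strong inference, but it is not stated.

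2. **Who is masked.** Randomization puts patients, study personnel and care providers on the unblinded side, and Muenster conducts the study. Only the independent evaluators are on the blinded side. The reading center is not mentioned there. The reason given for not blinding is the nature of the intervention. That reason does not reach the reading of an OCT or HRT image, which can be separated from the arm.

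3. **Where pseudonymization happens.** Data go from the ECF and the insurers to the trust center, are pseudonymized and merged there, and pass to the evaluating center. The article describes no coded route to the readers. The evaluators analyse the readers' results, so their blinding begins after the grade is given.

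4. **Whether grading involves judgement.** RNFL and rim values are instrument outputs. The article nevertheless requires evaluation by physicians, a junior and a senior reader, and a four-eye check, so it treats grading as more than copying a number.

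5. **Scope.** The planned sample is 990 × 2 = 1980 patients. With the planned 20% drop-out, 1980 × 0.80 = 1584 remain. At two examinations each, that is 1584 × 2 = 3168 patient-examinations with images to grade, assuming that all completers have OCT at both visits. HRT adds to this only where available.

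6. **The plausibility check.** It covers IOP. Under Primary endpoint, the self-tonometry arm has 7 days × 6 times = 42 scheduled measurements per eye. The inpatient arm has 6 per eye over the minimum 24 h, or 24 / 3 = 8 on the three-hourly schedule given in the Introduction. Either way, the length of the profile shows the arm to anyone who checks it, so this step cannot readily be masked. The article names no checker and gives no consequence for a reading judged implausible.

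7. **Sample size.** The plan's figure reproduces with a one-sided alpha of 0.05: n = (1.645 + 0.842)² × 2 × 0.20 × 0.80 / 0.05², which rounds up to 792 per group. Then 792 / 0.80 = 990. Nothing in this point changes those inputs.

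**The case against.** The strongest reply is that the article says nothing about reader masking either way, and that image de-identification is often described in a full protocol or a reading-center manual. No sentence says that the readers see the allocation or that graders and advisers are the same two people. The statement that images are evaluated for each patient group need mean only that both arms are graded. The structural measures are secondary and largely instrument-derived, and the article gives no basis for estimating how far a reader could move them.

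Much of this stands, and it limits the point to the absence of stated masking; unmasked reading is not shown. It does not dispose of the point. The article does set out a blinding scheme, saying who is and is not blinded, and it assigns grading to roles to which it also gives a care function. That is a stated arrangement as well as an omission.

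Three stronger readings are tempting and are not supported:

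- **The primary endpoint is biased by arm-aware rejection or acceptance of IOP readings.** The check has no named checker and no stated power to remove or change a value. A peak is a numeric threshold, 30% above a target set by the treating ophthalmologist.
- **About 40 altered patients (0.05 × 792 = 39.6) would use up the whole margin.** The arithmetic is right, but the shift is hypothetical. It assumes that one reading above the threshold makes a peak patient, which the article does not say. The direction is also open: rejecting high home readings would count against non-inferiority, and accepting false ones would favour it.
- **No senior reader is left to settle a doubtful case.** Letting each reader act as junior reader can equally mean two independent reads, and the reference to several physicians does not exclude a third.

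**Conclusion.** The point holds for the structural secondary outcomes. As written, RNFL thickness, BMO-MRW and the rim parameters at the initial and 12-month examinations are graded by roles that also advise on and supervise care, with no stated masking, although masking is feasible for images. This rests on reading the three role descriptions as the same pair and on the blinding scheme in Randomization being complete. Both are reasonable inferences, and neither is stated outright.

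The bias cannot be sized, because the article gives no reader variability and no expected structural difference between arms. For the primary endpoint no bias is shown and no magnitude is claimed. The IOP plausibility check justifies a precaution only.

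**What to change.** **Main change.** State in the protocol that the initial and 12-month images reach the readers under a code, in random order, without arm, clinical file or visit date, and that grades are locked before they are linked back to the ECF.

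**Secondary safeguard.** State the IOP plausibility check as numeric validity rules, fixed before data review and applied identically in both arms, with any excluded readings listed by arm.

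**Cost.** A coded image export and a short set of validity rules have to be programmed, and readers cannot consult the file while grading. Masking may be incomplete for patients on whom a reader has already advised, since that reader may have seen the images in the ECF. No additional reader is required for the coded export itself.

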### Statistical analyses

All statistical analyses will be performed using the current version of R/Rstudio and results will be presented following the CONSORT recommendations [36, 37]. Baseline characteristics (including sociodemographic and clinical data) will be analyzed using appropriate descriptive methods. These will include absolute and relative frequency distributions and measures of dispersion, such as median, mean, quantile, variance or standard deviation, used as appropriate, and visualized in a suitable form (e.g., boxplot or histogram). More precisely, baseline characteristics will be summarized for the IG and CG. Standard deviation (when assuming a Gaussian distribution), median, and interquartile ranges will be applied for continuous data (e.g., VFI or blood pressure) and frequencies or percentages will be used for binary data. After analyzing the entire cohort, subgroup analyses will be conducted to determine potential effect modifications (e.g., time effects, age or gender) on the primary endpoint.

The primary endpoint, percentage of detected peak values in IOP, will be analyzed using suitable inferential statistic methods (e.g., Mann–Whitney-*U* test for independent samples and assuming a normal distribution or odds ratios for binary outcomes). An appropriate regression model will be used to evaluate which regressor has an influence on the primary endpoint and residual analysis will be applied to test the results of the model for significance. Secondary endpoints will be evaluated using a similar analysis strategy while using appropriate models for the outcomes.

Data will be analyzed on the intention to treat principle (ITT). Thus, all participants who have given their informed consent will be included in the evaluation. More precisely, all patients of the IG and CG will need to be informed about the use of their data, and their willingness to participate must be ascertained and documented. Allocation to IG and CG as well as randomization will be conducted independently after recruitment of the study participants to ensure structural equality of the data between the two groups. To maintain this structural equality for data analysis, all participants will be evaluated according to the ITT principle as members of the treatment group to which they were randomized, whether or not the study participants used the allocated outpatient or inpatient method of measurement. Further, the potential amount and pattern of missing data will be defined, and if required, appropriate methods such as sensitivity analysis will be applied. This will allow accurate analysis of the assumptions and the effectiveness of self-tonometry in this study [38–40]. All models implemented will provide information on potential treatment effects and will be presented as a 95% confidence interval.

Following the recommendation of the German Institute for Quality and Efficiency in Health Care (IQWiG), the cost-minimization analysis will be carried out from the perspective of statutory health insurance and will, if applicable, be supplemented by analysis from a patient/societal perspective [41]. The economic analysis will conform to the principles of good secondary data analysis, the recommendations of the memorandum “Methods for Health Services Research,” and the standards of the German Evaluation Society [42–44].

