**Methods:**

The SALUS study is a randomized controlled, open non-inferiority trial, alongside an economic analysis, determining whether outpatient monitoring of IOP with self-tonometry is at least as effective as current standard care and would reduce treatment costs. Participants (*n* = 1980) will be recruited by local ophthalmologists in the area of Westphalia-Lippe, Germany, and randomized to receive 7-day outpatient or 24-h inpatient monitoring. Participants in both study arms will also receive 24-h blood pressure monitoring. Furthermore, patient data from both study groups will be collected in an electronic case file (ECF), accessible to practitioners, hospitals, and the study participants. The primary endpoint is the percentage of patients with IOP peaks, defined as levels 30% above the patient-specific target pressure. Data will also be collected during initial and final examinations, and at 3, 6, and 9 months after the initial examination.

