More specifically, the SALUS study aims to demonstrate that self-tonometry is non-inferior to the established 24-h inpatient IOP measurements for monitoring and treating glaucoma. The primary hypothesis in this non-inferiority trial is that the percentage of patients in whom pressure peaks could be detected during the pressure profile would not differ significantly between the intervention group (IG = outpatient self-tonometry) and the control group (CG = inpatient measurement every 3 h over the course of 24 h). In this study, a pressure peak was defined as a level 30% above the patient-specific target pressure which will be set by the treating ophthalmologists. The health economic hypothesis tests whether the use of self-tonometers reduces costs from a healthcare provider perspective compared to current standard care.

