## Materials and methods

### Study design

The SALUS study is a multicenter, two-arm parallel group, open non-inferiority, randomized controlled trial with an economic analysis alongside.

This non-inferiority design was chosen to establish that outpatient monitoring of IOP with self-tonometry is not less effective than standard care with hospitalized monitoring of IOP. The trial will be conducted in hospitals and patients’ homes in the district of Westphalia-Lippe, Germany. Each participant will be followed for 12 months from the start of the trial, with regular follow-up every 3 months by local ophthalmologists (see Fig. 1).

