### Sample size

The sample size was determined using the license-free software “R” (R v. 3.6.3, Rstudio v. 1.2.5042). The estimation of sample size and power analysis is based on the primary endpoint “exceeding patient-specific target pressure”. As null hypothesis, it is assumed that the proportion of pressure peaks in IG is smaller than the proportion in CG (i.e., non-inferiority).

Based on clinical experience, a margin of 20% is assumed for detection of IOP fluctuations and peak values in both groups. A non-inferiority margin of *δ* = 0.05 is acceptable, meaning the proportion of pressure peaks in self-tonometry should fall below the proportion in 24 h IOP by more than 5% to be taken as a statistically significant difference [34, 35]. With regard to the probability of type I and II errors, significance levels will be set at *α* = 0.05 and *β* = 0.2, respectively, i.e., a power of (1 − *β*) = 0.8. This results in a total of 1584 patients (792 per group). After adjusting for a drop-out rate of 20%, a final sample size of 1980 patients (990 per group) will be required for this trial (see Fig. 2).

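### The example methods for the primary endpoint (Mann–Whitney U test, odds ratios) do not match the non-inferiority hypothesis, with its absolute 0.05 margin, on which the trial was sized

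*Protocol article*

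**What the plan says.** The Study design section describes a "multicenter, two-arm parallel group, open non-inferiority, randomized controlled trial". The abstract defines the endpoint per patient: "The primary endpoint is the percentage of patients with IOP peaks, defined as levels 30% above the patient-specific target pressure". The Sample size section says that "a margin of 20% is assumed for detection of IOP fluctuations and peak values in both groups", sets δ = 0.05 and explains it with the words "meaning the proportion of pressure peaks in self-tonometry should fall below the proportion in 24 h IOP by more than 5" per cent to count as a statistically significant difference. It gives α = 0.05 without saying whether this is one- or two-sided, power 0.8, 792 patients per group, and 1980 in total after 20% drop-out.

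The Introduction words the primary hypothesis differently: the percentage of patients with detected peaks "would not differ significantly between the intervention group" and the control group.

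The Statistical analyses section says that suitable methods will be used for the primary endpoint. As examples it gives a Mann–Whitney U "test for independent samples and assuming a normal distribution or odds ratios for binary outcomes". A regression will then look for influential regressors, and "residual analysis will be applied to test the results of the model for significance". The same section says that model effects will be presented with 95% confidence intervals. It does not relate any interval to the 0.05 margin.

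**The concern.** A non-inferiority claim needs an estimate on the scale of the margin and a confidence limit to compare with it. Neither printed example provides this directly.

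- The Mann–Whitney U test is a rank test. It does not assume a normal distribution, so its description is wrong. On a yes/no outcome it is in effect the chi-square test of no difference, and no margin enters.
- An odds ratio is on a different scale from an absolute difference of 0.05. The limit it would have to clear depends on the control rate, and the article states no conversion.
- The Introduction's wording invites the reader to take a non-significant result as success. So does the Sample size section, which explains the margin in terms of statistical significance.

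At stake is the trial's main conclusion. A test of no difference can give the opposite answer to a comparison with the margin.

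**Working it through.** **Inputs.** From Sample size: 20% in both groups, δ = 0.05, α = 0.05, power 0.8, 792 per group, 20% drop-out. From Randomization: 1:1 allocation.

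**1. Reproduce the sample size and so identify the scale.**
n per group = (z₁₋α + z₁₋β)² × [p(1−p) + p(1−p)] / δ²
= (1.645 + 0.842)² × 0.32 / 0.0025 = 791.4 (unrounded z-values), so 792. This matches.
Total 1584; 1584 / 0.8 = 1980. This matches.
Other readings do not match. One-sided 2.5% gives 1005 per group. A no-difference test of 20% v 15% gives 906 (two-sided) or 714 (one-sided). The margin is therefore an absolute difference in proportions, and the level used was one-sided 5%.

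**2. The odds ratio that corresponds to a 5-point deficit.**
OR = [(p_C − 0.05)/(1 − p_C + 0.05)] / [p_C/(1 − p_C)]

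| Control rate | OR at the margin |
|---|---|
| 10% | (0.05/0.95)/(0.10/0.90) = 0.47 |
| 20% | (0.15/0.85)/(0.20/0.80) = 0.71 |
| 30% | (0.25/0.75)/(0.30/0.70) = 0.78 |

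Conversely, a limit fixed at OR 0.706 (the 20% value) would tolerate a loss of 2.7 points at a 10% control rate and 8.6 points at 50%.

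**3. If non-significance were read as success.** Take a true 15% v 20%, 792 per arm, two-sided 5% test.
SE under no difference = √(2 × 0.175 × 0.825 / 792) = 0.01909.
SE under the true rates = √((0.15 × 0.85 + 0.20 × 0.80) / 792) = 0.01905.
P(significant) = Φ[(0.05 − 1.96 × 0.01909)/0.01905] = Φ(0.66) = 0.745.
P(not significant) = 0.255, about 25%, against the 5% for which the trial was sized.

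**4. The two approaches can disagree** (illustrative counts, simple Wald intervals).
- IG 137/792 v CG 158/792: Mann–Whitney p = 0.175 and chi-square p = 0.175, so not significantly different. The difference is −2.7 points, 95% CI −6.5 to +1.2, one-sided 95% limit −5.9. Non-inferiority is not shown.
- IG 30/792 v CG 50/792: p = 0.022, so significantly different. The 95% CI is −4.7 to −0.4, so non-inferiority is met. This reversal needs rates well below the assumed 20%: (1.96 + 1.645) × SE must be under 0.05, which at 792 per arm means rates below about 8%. The first example is the practical risk.

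**5. Interval level.** SE at 20% in both arms = √(0.32/792) = 0.0201, and 0.05/0.0201 = 2.488.
- One-sided 95% limit (two-sided 90% interval): Φ(2.488 − 1.645) = 80.0%.
- Two-sided 95% interval: Φ(2.488 − 1.960) = 70.1%. Keeping 80% would need 1005 per arm, or 2010 evaluable and 2010/0.8 ≈ 2513 randomised.

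**The case against.** The strongest defence is that the methods are only examples and that a separate analysis plan may name the right one. The Sample size section does give a margin, and the promised 95% intervals could serve if put on the risk-difference scale. This has force. A reader might infer that the trial is committed to an analysis that can neither establish nor refute non-inferiority, but the text leaves the estimator open and does not exclude a risk difference. Nor is the absence of a named interval method a fault in a journal article. What remains is that the examples printed are wrong for the stated hypothesis, which is a misstatement and not a gap.

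A reader might also class the odds ratio as a test of no difference. It is an effect measure, and its interval could be set against a margin converted at a stated control rate. The defect is only that it cannot be compared directly and that no conversion is given.

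It could be argued that elsewhere the article speaks of the percentage of peak values, not of patients, and that a rank test would suit a percentage calculated for each patient. It would still carry no margin and would not match a sample size calculated for proportions of patients.

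Finally, the residual-analysis sentence belongs to the regression on influential factors and does not bear on the non-inferiority decision. It is a wording error of minor weight.

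**Conclusion.** The point holds as a mismatch between the printed example methods and the hypothesis that was sized. That the margin is an absolute difference rests on the exact reproduction of 792 per group. The odds-ratio equivalents of 0.47, 0.71 and 0.78 follow from arithmetic alone.

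The 25% figure is conditional. It assumes a true 15% v 20%, 792 evaluable patients per arm, a two-sided 5% test and a reading of non-significance as non-inferiority. The article states no such decision rule; the Introduction's wording only leans towards it. The figure is therefore the size of the risk if that wording were followed, not the trial's error rate.

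The power figures of 80% and 70% assume 20% in both arms.

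A reader might also infer that adjusting for enrolment IOP relative to target pressure would bring a known gain in power. The documents do not support this. Table 2 marks IOP at enrolment, but nothing says that the target is fixed by then, and no figure is given for how well the ratio predicts a peak.

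**What to change.** - State the primary analysis as the risk difference (IG − CG) in the proportion of patients with a peak, with a score-type confidence interval (Miettinen–Nurminen or Newcombe). Non-inferiority is shown if the lower limit is above −0.05.
- State the interval level. A one-sided 95% limit matches the sample size as calculated. If a two-sided 95% interval is intended, acknowledge about 70% power at 792 per arm or revise the sample size.
- Reword the hypothesis in the Introduction, and the explanation of the margin under Sample size, to match this rule.
- Drop the Mann–Whitney test for this endpoint, keep odds ratios as supportive, and describe residual analysis as model checking only.
- Optionally, use a covariate-adjusted risk difference by standardisation from a logistic model, restricted to covariates confirmed to be recorded before randomisation and without a claimed gain in power.

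The cost is wording in the protocol and analysis plan. The methods are available in R, which is already planned. The number of patients does not change if the one-sided 95% limit is used.
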